### Training of HCPs/researchers to deliver the Snacktivity™ intervention

Those delivering the intervention will be trained by the research team to deliver the Snacktivity™ intervention following a standard protocol; we have developed a media-based training module that can be delivered face-to-face or remotely. We anticipate the training will take no more than 1 h given the involvement of HCPs/researchers is simple and brief. The training tools will include information on the importance of adhering to the study protocol, the research study procedures, trial design and ways of delivering the Snacktivity™ intervention. More specifically, the training aims to demonstrate different ways in which Snacktivity*™* can be promoted by HCPs within the consultation (where appropriate). We have also developed video clips that show Snacktivity™ being delivered in GP practices, so that HCPs have an understanding of how the intervention might be delivered by them.

### Intervention fidelity and contamination

With the consent of participants, the delivery of the Snacktivity™ information will be audio-recorded to assess for fidelity against the intervention component checklist. Those delivering the intervention will be trained on the importance of delivering the correct information to participants according to their randomised group to minimise the possibility of contamination. The Fitbit device and SnackApp will only be available to participants randomised to the intervention group. A range of the strategies to reinforce intervention fidelity will be used. We will.Develop a standardised training resource.Train HCPs/researchers to deliver the intervention according to the protocol.Explain the intervention logic model to HCPs/researchers.Audio record all consultations and telephone calls with a researcher to assess whether the intervention is being delivered according to the intervention checklist (with participant consent).Check for intervention ‘receipt’ and enactment by checking whether participants attended their consultation and whether the physical activity self-monitoring device and SnackApp™ are activated.

### Comparator group

We are not proposing any change to standard care. The usual care group will therefore receive the normal physical activity advice and any typical behavioural change strategies adopted by HCPs within consultations. The usual care group will only receive the current guidance for physical activity (to achieve 150 min of MVPA) within their healthcare consultation or during the telephone call with a researcher, who will advise they work towards the accumulation of at least 150 min MVPA per week. Participants will also receive a leaflet. With the consent of participants, the delivery of the usual care information will be audio-recorded to assess fidelity and intervention contamination.

### Primary outcome

The primary outcome is the feasibility and acceptability of a subsequent phase III RCT according to pre-specified progression criteria. We are primarily interested in whether the Snacktivity™ intervention and trial are appealing to participants (assessed by the recruitment rate) and if the Snacktivity™ intervention and the evaluation methods are acceptable to participants (measured by Snacktivity™/physical activity adherence and retention rates). We also wish to assess the recruitment and randomisation processes, measure the extent of any intervention contamination, and use data collected in the feasibility trial to review the sample size assumptions for the phase III trial.

### Progression criteria for phase III trial and stop–go criteria

The decision of whether to continue to the phase III trial will be guided by the assessment of the data collected during the feasibility trial (both quantitative and qualitative). For the quantitative data (Table 1), the following pre-defined stop–go criteria will be used:*Recruitment*: defined as the number/percentage of people randomised against the recruitment target of 80 participants over 5 months.Snacktivity*™ adherence*: defined as the number of physical activity snacks achieved (defined as minimum of four bouts of MVPA lasting ≥ 2 min on average each day over 12 weeks) assessed by the Fitbit monitoring device (in the Snacktivity*™* arm only).*Physical activity adherence*: defined as the proportion of participants who are accumulating a total weekly average of at least 105 min of MVPA (~ 15 min daily) (in the Snacktivity*™* arm only).*Attrition*: defined as withdrawal from the trial and/or no follow-up data available.

**Table 1 Tab1:** Traffic light criteria

Green	At least 80% of the target sample size is recruited
	At least 65% of the intervention group are achieving Snacktivity™ adherence
	At least 60% of the intervention group are achieving physical activity adherence
	Attrition < 21%
If all four criteria are met, we will proceed to the full trial with the protocol unchanged (unless there is a clear indication from the qualitative interviews and our experience that would improve the protocol)	
Amber	50–79% of the target sample size is recruited
	45–64% of the intervention group are achieving Snacktivity™ adherence
	45–59% of the intervention group are achieving physical activity adherence
	Attrition 21–35%
If one or more of our amber criteria are met, we will plan to adapt the protocol in light of the results of the feedback from the qualitative interviews and our experience to improve which ever criteria are not at the ‘green light’ level before proceeding to the full trial	
Red	< 50% of the target sample size is recruited
	< 45% of the intervention group are achieving Snacktivity™ adherence
	< 45% of the intervention group are achieving physical activity adherence
	Attrition > 35%
If one or more of these criteria are met, we would consider the current protocol not feasible and not progress to the phase III RCT with the current protocol	

### Secondary outcomes

Data will be collected on outcomes that we plan to collect in the definitive RCT at baseline and follow-up (see Table 2). While this feasibility trial is not powered to detect meaningful differences in these outcomes, collecting this data means we can assess and ensure that there are no issues with the collection and completion of these measures in preparation for the phase III trial. We will calculate MVPA, total physical activity, light physical activity, sedentary time (i.e. inactive time during waking hours), and sleep (and other metrics that may become available through novel processing methods) using data collected from a wrist worn research grade blinded accelerometer on participants’ non-dominant wrist (Axivity AX3; Axivity, Newcastle, UK) for at least seven days in both groups. A self-reported wake and sleep times log will be completed during the same days the accelerometer is worn. Other data collected at baseline and follow-up in all participants include self-reported sedentary behaviours (using the Workforce Sitting Questionnaire (WSQ) [36] and the sedentary behaviour item from the International Physical Activity Questionnaire [37], lower limb muscle strength (Takei dynamometer squat position), weight, waist circumference, blood pressure, and depression/anxiety (Hospital Anxiety and Depression Scale) [38], Physical Activity Enjoyment Scale [39] and Exercise Self-efficacy Questionnaire [40]. The Self-Report Habit Index [41] and a checklist of popular activity snacks questionnaire (Snacktivity™ checklist) are completed at follow-up in the intervention group only. Participants’ experiences of the trial will be captured in single item exit questions at follow-up, which includes questions relating to contamination. Specifically, participants are asked whether they know anyone else taking part in the study, and if so, whether they discussed the study with them.

**Table 2 Tab2:** Schedule of assessments

Visit	Screening	Baseline visit (− 7 + 14 days)	Follow-up (12 weeks) (− or + 14 days)
Expression of interest	x		
Physical activity status: General Practice Physical Activity Questionnaire) [27]	x		
Eligibility screening telephone call	x		
Personal identifiers and demographic information		x	
Current medications			x
Smoking history		x	
Alcohol consumption		x	
Mobility		x	
Diseases/conditions		x	x
Wrist worn accelerometer (worn for up to 8 days) (axivity)		x	x
Anxiety and depression: HADS [38]		x	x
Healthcare utilisation			x
Household income/composition			x
Productivity			x
Sedentary behaviours: Workforce Sitting Questionnaire [36] and sedentary behaviour item from the International Physical Activity Questionnaire [37]		x	x
Enjoyment of physical activity: Physical Activity Enjoyment Scale [39]		x	x
Self-efficacy for exercise and Exercise Self-efficacy Questionnaire [40]		x	x
Habit strength (Snacktivity*™* group only): The Self-Report Habit Index [41]			x
SnackApp™ engagement analytics (Snacktivity*™* group only)			x
Height^a^		x	
Weight		x	x
Body mass index (BMI)		x	x
Waist circumference		x	x
Lower limb muscle strength (Takei dynamometer squat position)		x	x
Blood pressure		x	x
Checklist of popular snacks (paper copy, Snacktivity*™* group only)			x
Semi-structured interviews (Snacktivity*™* intervention group and health care providers)		x	x
Single item study feedback questions			x

^a^To allow for the calculation of BMI, height will be measured to the nearest 0.1 cm using SECA 213 stadiometers at baseline and follow-up

We plan to conduct a cost effectiveness study in the subsequent phase III trial and the questionnaire items to be used to assess health care resource use and productivity will be piloted in this feasibility trial. The physical activity self-monitoring device (Fitbit) will provide the following data for participants in the intervention group; steps, distance, calories, bouted active minutes, inactive time, sleep and awake time, and wear time (through body sensor). The Snacktivity™ active minutes will be computed from Fitbit device measured METs and activity snacks.

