## Aims and objectives

Whilst the idea that small bouts of physical activity may improve health is not new, it is not a message that has been highlighted to the public, in part, because of a lack of robust evidence in real world health settings. To date, no randomised controlled trial (RCT) has directly investigated whether Snacktivity™ increases participation in MVPA or the number of people meeting the recommended guidelines for physical activity. The primary aim of the Snacktivity™ research programme is to evaluate the clinical and cost effectiveness of the Snacktivity™ intervention for increasing and maintaining physical activity by undertaking a large multicentre RCT. However, first we need to undertake a randomised feasibility trial with nested qualitative interviews to assess the feasibility and acceptability of the Snacktivity™ intervention and the methods needed to conduct the phase III randomised trial. We are seeking to test a complex intervention and there are uncertainties, specifically regarding recruitment methods and rates, intervention adherence and participant retention, that need to be assessed before undertaking a large-scale RCT.

This feasibility trial aims to:Examine the recruitment rate to inform the planned phase III trial.Provide data to review and inform the sample size assumptions for the phase III trial.Assess the data collection methods, data completeness and retention rates.Investigate the feasibility and acceptability of the Snacktivity™ intervention to the public and health care providers (HCPs) delivering the intervention.Assess adherence to the Snacktivity™ interventionGather data to refine the Snacktivity™ intervention and assess intervention delivery fidelity.Examine the potential for intervention contamination, to inform the decision to use individual randomisation over a cluster RCT.Assess acceptability of the intervention training materials and procedures for HCPs.

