### Recruitment of participants

Participating general practices and NHS Trusts will search their electronic records to identify patients who are ≥ 18 years and have a health care consultation booked during the recruitment phase of the trial. These individuals will be sent a consultation appointment letter (or reminder of the upcoming appointment), along with the trial invitation letter, participant information sheet (PIS), expression of interest form (EOI) and the General Practice Physical Activity Questionnaire (GPPAQ) for screening physical activity status [27]. Those classed as inactive/moderately inactive/moderately active according to the GPPAQ (based on questions 1, 2a, and 2b) will be contacted by telephone to complete eligibility screening with a member of the research team. If a general practice or NHS Trust service routinely uses, or wishes to use, Short Message Service text messages to send patients details of their scheduled appointments and/or to notify them about this study, a study invite link will be added to these text messages where the trial documents referred to above can be accessed by those interested in taking part.

Clinicians/HCPs can also raise the topic of the Snacktivity™ study in routine consultations and those interested in discussing the trial further will be asked to complete the EOI form and GPPAQ, which will be passed on to the research team and these potential participants will complete eligibility screening with the research team by telephone. Potential participants can also be invited to take part in the study via community settings, including social media. These participants will either be sent the recruitment packs in the post or asked to complete the study documents electronically via the study invitation link as detailed above.

For all routes of recruitment, potentially eligible participants will be contacted by telephone by a member of the research team to complete further and final eligibility screening (see below for the full list of criteria applied). If eligible, a baseline visit will be booked to collect assessment data. For participants recruited via a reminder letter this will take place prior to participants’ health/intervention consultation appointment.

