To facilitate habit formation the SnackApp™ will generate regular reminders and notifications for the intervention group to engage in Snacktivity™. Self-monitoring may be particularly relevant for developing Snacktivity™ habits because it may be more difficult for people to easily recall how many activity snacks they have achieved each day. The design and content of the SnackApp™ is based on previous work packages, some of the principals of existing apps, and our previous experiences of developing apps for promoting physical activity and lifestyle behaviours. Participants will receive free access to the SnackApp™ after their consultation, which, within its functions, will contain features common in digital health interventions. Within these functions, the SnackApp™:Automatically captures/monitors daily physical activity and inactive time via a wrist worn consumer monitor (Fitbit Versa 2 device). It provides measures of steps, activity level, inactivity and energy expenditure each minute. A companion SnackApp™ will be downloaded onto the clock face of the Versa to allow instantaneous feedback on Snacktivity™ progress throughout the intervention period.Classifies participants into an activity profile according to their active and inactive time.Provides physical activity prompts after user-defined inactive periods, encouraging regular active snacks throughout the day.Generates individualised motivational push notifications to participants’ mobile phones based on prior behaviour and supports goal setting (both automatic and user-defined).Provides individualised feedback related to goal achievement to encourage adherence and facilitate self-efficacy. Individualised feedback will be provided on the accumulated number of physical activity snacks completed and total minutes ‘activity snacking’ per day, progress towards meeting the recommended level of physical activity for health benefits (150 min of MVPA per week) and the total number of minutes of physical activity, MVPA and the number of steps each day.Enables access to educational content (text, static images, video, and audio content) regarding Snacktivity™, both externally hosted and supplied by the research team, including examples of activity snacks (with instructive photos and gifs)Encourages social support via a forum to facilitate a Snacktivity™ social community.To promote habit formation, users will be able to plan when to perform activity snacks.

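### The contamination exit questions do not record the other person's arm, so a usual-care yes cannot be read as exposure to the intervention

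*Protocol article*

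**What the plan says.** Contamination is a stated aim of the feasibility trial. Aims and objectives lists: "Examine the potential for intervention contamination, to inform the decision to use individual randomisation over a cluster RCT". Primary outcome repeats the intention to "measure the extent of any intervention contamination". Randomisation and blinding says that individual randomisation has been chosen, that the contamination risk is expected to be low, and that it will be assessed.

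Two sources of contamination data are described.

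- **Exit questions (Secondary outcomes).** Trial experiences are "captured in single item exit questions at follow-up, which includes questions relating to contamination". The content is then specified: "participants are asked whether they know anyone else taking part in the study, and if so, whether they discussed the study with them". No restriction to one arm is stated, although other items in that section are marked as intervention group only.
- **Audio recordings (Comparator group).** Delivery of usual care is recorded, with consent, to assess fidelity and contamination.

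The app includes a forum: "Encourages social support via a forum to facilitate a Snacktivity™ social community". Intervention fidelity and contamination states that the app and the Fitbit go to the intervention group only.

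**The concern.** Contamination here means that a usual-care participant is exposed to Snacktivity content. The exit questions establish that two participants know each other and that they talked about the study. Two usual-care friends, two Snacktivity friends and a cross-arm pair would all give the same pair of answers. Only the cross-arm pair is contamination, and only the usual-care member of it is the one exposed.

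The missing fact is the arm of the contact. Later analysis cannot recover it if it was never asked, so a counting rule in a statistical analysis plan would not repair the gap.

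At stake is one input to a design decision for phase III. If some usual-care participants answer yes, the investigators will not know how many of those answers bear on individual versus cluster randomisation.

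**Working it through.** **Is there a figure to reproduce?** No. The protocol gives no contamination rate, threshold or counting rule. The check therefore asks what a usual-care yes can mean, and how far it could depart from cross-arm contact.

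**Inputs.** Target 80 participants (Statistical considerations and data analysis) and 1:1 individual allocation (Randomisation and blinding), hence 40 per arm. Assumptions: acquaintance is independent of arm, and a respondent who answers yes has discussed the study with all k participants they know.

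**Step 1: one contact each.** A usual-care participant has 79 possible contacts, of whom 40 are in the Snacktivity arm and 39 in usual care.

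- Cross-arm share: 40/79 = 50.6%. Same-arm share: 39/79 = 49.4%.
- Ratio of yes answers to cross-arm contact: 79/40 = 1.975 (given here as 1.97).
- If the 72 participants reported under Trial progress were split evenly, the share would be 36/71 = 50.7%, so the result hardly depends on reaching 80.

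**Step 2: several contacts.** The chance that at least one of k contacts is in the Snacktivity arm is 1 − C(39,k)/C(79,k), and the ratio is its reciprocal.

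| Contacts k | P(at least one Snacktivity contact) | Ratio of yes answers to cross-arm contact |
|---|---|---|
| 1 | 0.506 | 1.97 |
| 2 | 0.759 | 1.32 |
| 3 | 0.884 | 1.13 |

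The ratio falls as contacts increase, so 1.97 is the largest of the three and not a floor.

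**Step 3: an illustration.** The documents give no contact rate, so take 10% as an assumption. Then 4 of 40 usual-care participants answer yes with one contact each. The expected number with a cross-arm contact is 4 × 40/79 = 2.0, or 5.1% of the arm.

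**Step 4: the forum.** Only Snacktivity participants have the app, so forum contact is same-arm by design. It can produce a yes in the intervention arm but never in usual care. Each respondent's own arm is known, so tabulating answers by arm removes the forum from the usual-care figure. The same-arm contact in steps 1 and 2 remains.

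**Step 5: what the questions cannot see.** A provider or researcher who delivers both messages may pass intervention content to a usual-care participant. The exit questions miss this. Let t be true cross-arm contact and h provider-mediated contamination, independent of each other. Raw yes answers (proportion y) equal total contamination when 1 − (1 − t)(1 − h) = y, so h = 1 − (1 − y)/(1 − t), with t = y × 40/79.

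| Usual-care yes, y (assumed) | t | Break-even h |
|---|---|---|
| 5% | 2.5% | 2.5% |
| 10% | 5.1% | 5.2% |
| 20% | 10.1% | 11.0% |

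Below the break-even value, raw yes answers overstate total contamination; above it, they understate it.

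**Step 6: does another described source fill the gap?** The recordings capture what is said in a consultation or call, not later conversation between participants. The schedule of assessments lists interviews with the Snacktivity group and health care providers only. The habit index and snack checklist are for the intervention group only. The accelerometer is worn in both arms but cannot show why activity changed. The exit questions are thus the only described measure of participant-to-participant contamination in usual care.

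**The case against.** The strongest reply is that nothing in the protocol turns a yes into a contamination count. No counting rule is given and no pooling of arms is stated for these questions; the analysis section pools recruitment and attrition only. A reader might infer that contamination will be overstated, perhaps without limit because of the forum. The documents do not support that. Forum contact cannot reach usual-care answers, it is not established that forum users would say they know each other, and step 5 leaves the net direction open. This part of the reply stands.

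A second reply is that the stakes are modest. The data inform the randomisation decision and do not settle it. Individual randomisation is already chosen, partly so that people outside health services can be recruited, and contamination is not among the four stop–go criteria. This also stands and keeps the point small.

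A third is that the article condenses a questionnaire that is not shown. That is a fair caution: further wording may exist. But the article goes beyond a general mention and specifies the content, and the contact's arm is not part of it. If the full questionnaire already asks for the arm, the point is met.

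Finally, a reader might treat contact within a household as over-counting. If the two people are in opposite arms and discuss the study, that is real contamination and belongs in the count.

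**Conclusion.** The point holds in a limited form. As described, the exit questions cannot separate a usual-care participant's contact with a Snacktivity participant from contact within usual care, and no other described source does so. Read raw, usual-care yes answers would exceed cross-arm contact by about 1.97-fold with one contact each, 1.32-fold with two and 1.13-fold with three. These factors rest on 40 per arm and on acquaintance being independent of arm. The second is an assumption that minimisation on route, age and gender could disturb. The number of contacts and the contact rate are unknown.

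Intervention-arm answers may reflect same-arm forum contact and should not be read as contamination. No direction of bias can be claimed for total contamination. This is a cheap improvement to one measure and does not threaten the trial's progression decision.

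**What to change.** For participants who answer yes, add two tick-box items at follow-up:

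1. Which group was that person in: Snacktivity, usual care, don't know?
2. How do you know them: household, work, same practice or provider, SnackApp forum, other?

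Define the peer-contact measure as the number of usual-care participants who discussed the study with a Snacktivity participant, divided by usual-care responders. Show the don't-know answers separately. Report intervention-arm answers apart and do not count them as contamination. Read the result alongside the usual-care recordings, which cover the provider route. The second item helps to judge which contacts a cluster design would remove.

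The article reports follow-up as ongoing, so the items can be used for any remaining follow-up visits and carried into phase III. If only some participants are asked, state the reduced denominator.

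The cost is two short items, one line of analysis and some don't-know answers. Participants are told their allocation after baseline, so many could pass it on to a contact.
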